# Create a DataFrame with your Riley results
'''## R Riley's Method
library(pmsampsize)
parameters <- 1:20
sample_sizes <- vector("list", length(parameters))
# Loop over each parameter value
for (i in parameters) {
  # Call pmsampsize with the current parameter and store the result in res
  res <- pmsampsize(type = "s", csrsquared = (0.88 - 0.5)^2 / 0.75, parameters = i,
    rate = 0.24,timepoint = 10, meanfup = 10)

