### Riley’s Method

Riley’s method is an advanced approach that calculates the required sample size by considering model performance parameters and anticipated shrinkage. Using the R package *pmsampsize*, we computed the required total sample size for a range of candidate predictor numbers (denoted by  $k$ ). The calculations incorporated the following parameters:

- A candidate model’s anticipated performance was characterized by a global  $R^2$ , which was derived using the formula:

$$R_{CS}^2 = \frac{(R_{app} - 0.5)^2}{0.75}$$

where  $R_{app}$  represents the apparent  $R^2$  (in our case, 0.88).

- An expected event rate of 25% was assumed.

- A time horizon of 10 years for the outcome and a mean follow-up of 10 years were specified.

For each value of  $k$ , Riley's method provided an estimate of the required total sample size to achieve a pre-specified level of predictive performance while controlling for overfitting. These estimates were then compared across values of  $k$ .

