### EPV-Based Sample Size Calculation

In parallel, we applied the widely used rule-of-thumb based on the events per variable (EPV) criterion. According to this approach, a minimum number of events per predictor is required to reliably estimate model parameters. The required number of events  $D$  is given by:

$$D = EPV \times k$$

where EPV is typically set to 10 (or adjusted to 11 or 12 in sensitivity analyses) and  $k$  represents the number of candidate predictors. Given an expected event rate (denoted as  $\lambda$ ), the total required sample size  $N$  is then calculated as:

$$N = \frac{D}{\lambda} = \frac{(EPV \times k)}{\lambda}$$

For example, assuming an event rate of 25%, the total sample size for an EPV of 10 would be computed as:

$$N = \frac{10 \times k}{0.25}$$

This calculation was performed across a range of  $k$  values, and similar computations were repeated for EPV values of 11 and 12 to assess the sensitivity of the sample size requirement (Figure 2).

In our study, we assumed:

- an expected event rate of 25% (i.e., 0.25),
- candidate predictor numbers ranging up to 15, and
- performance parameters as specified by the global  $R^2$ , where  $R_{app}$  equal to 0.88

The required total sample sizes were:

- EPV = 10: sample size = 640,
- EPV = 11: sample size = 704,
- EPV = 12: sample size = 768.
- Riley's method sample size = 782

Based on these estimates, we ultimately adopted a sample size of 700 participants. This choice is consistent with our initial sample size estimation for protein screening and is expected to provide sufficient power for robust predictive modeling while minimizing the risk of overfitting. The pseudo code is as follows:

```

import math
import numpy as np
import pandas as pd
import matplotlib.pyplot as plt
#####

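### SAP 8.2 gives the Riley calculation a Cox-Snell R-squared from an invalid conversion; a valid input could move the modelling requirement either way, so it needs restating

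*Combined protocol and SAP*

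**What the plan says.** SAP 8.2 (Riley's Method) derives the Cox-Snell R-squared by subtracting 0.5 from a quantity R_app, squaring, and dividing by 0.75. It calls R_app the apparent R-squared and sets it ("in our case, 0.88"). The R code passes the result on as "csrsquared = (0.88 - 0.5)^2 / 0.75, parameters = i". No source or derivation is given.

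The other inputs are stated as follows.
- Event rate: "An expected event rate of 25% was assumed" in the text, but "rate = 0.24,timepoint = 10, meanfup = 10" in the code.
- Horizon: "A time horizon of 10 years for the outcome and a mean follow-up of 10 years were specified".
- Predictors: "candidate predictor numbers ranging up to 15, and". The result "EPV = 10: sample size = 640" implies 640 × 0.25 / 10 = 16, and the figure legend says 17.
- Target shrinkage: not stated.

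The section then reports "method sample size = 782", adopts 700 participants, and says that this size keeps overfitting to a minimum. Supplementary Table 1 shows that 680 were used for training.

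**The concern.** The Riley method asks how many participants are needed for a model of given expected performance to be fitted with little overfitting. Performance enters as the Cox-Snell R-squared, 1 − exp(−LR/n), where LR is the likelihood-ratio statistic. For a given strength of prediction, that quantity depends on how many participants have events.

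The SAP's expression has no event term, and it does not behave like a conversion between R-squared values. Subtracting 0.5 makes sense only for a C-index or AUC, which the text does not mention. The word apparent normally means in-sample, whereas the method needs performance expected in new data. That matters here because SAP 6.4.2 describes a search over about one million protein combinations.

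At stake is the statement that 700 participants suffice for modelling. It cannot be checked against a figure whose performance input is undefined.

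**Working it through.** **Inputs.** R_app = 0.88; rate 25% (text) or 0.24 (code); mean follow-up 10 years; k = 15, 16 or 17 (all SAP 8.2). Observed composite event share 17.98% (SAP 3). Assumed, because the SAP gives neither: target shrinkage S = 0.9, and permitted optimism of 0.05 × maximum R-squared.

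**Formulas.** With R2 the Cox-Snell value and e the events per person (rate × mean follow-up):
- Shrinkage criterion: n = k / [(S − 1) ln(1 − R2/S)].
- Optimism criterion: the same n with S = R2 / (R2 + 0.05 × max R2), where max R2 = 1 − exp[2(e ln e − e)].
- The requirement is the larger of the two. The third criterion, precision of the 10-year risk, did not govern in the cases checked.

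**1. The conversion.** (0.88 − 0.5)² / 0.75 = 0.1444 / 0.75 = 0.1925. The same expression at other inputs:

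| R_app | 0 | 0.12 | 0.5 | 0.88 | 1 |
|---|---|---|---|---|---|
| Result | 0.333 | 0.1925 | 0 | 0.1925 | 0.333 |

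It is not monotone and cannot exceed 0.333. At e = 0.25, max R2 is 0.697, so 0.88 cannot itself be a Cox-Snell value at the planned event share.

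**2. Reproducing 782.** Take k = 15 and R2 = 0.1925, and read 25% as a yearly rate over 10 years, so e = 2.5.
- max R2 = 1 − exp[2(2.5 × 0.9163 − 2.5)] = 0.342.
- S = 0.1925 / (0.1925 + 0.0171) = 0.918.
- Optimism criterion: n = 781.7, rounded up to 782. The shrinkage criterion gives 624, so optimism governs.

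A constant yearly rate of 0.25 implies a 10-year risk of 1 − exp(−2.5) = 92%, not 25%. The printed code has 0.24 (e = 2.4). For k = 15 that gives 593 by optimism and 624 by shrinkage, so the code as printed returns 624, not 782.

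**3. Event share as a proportion.** At e = 0.24, 0.25 or 0.18 the shrinkage criterion governs at R2 = 0.1925. For k = 15, n = 15 / [0.1 × (−ln(1 − 0.1925/0.9))] = 623.2, rounded up to 624. For k = 16 and 17 it gives 665 and 707.

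**4. Sensitivity to R2.** Staying with the SAP's expression at k = 15, moving 0.88 to 0.86 takes 624 to 704, and moving it to 0.80 gives 1,049.

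**5. If 0.88 is a C-index.** I simulated data with a normal linear predictor, exponential event times, and censoring uniform over 1 to 12 years capped at 10 (all assumptions). I took R2 = 1 − exp(−LR/n) and the larger of the two criteria at k = 15:

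| C | R2, 18% events | n | R2, 25% events | n |
|---|---|---|---|---|
| 0.75 | 0.151 | 820–860 | 0.190 | 640 |
| 0.80 | 0.213 | 550–560 | 0.273 | 415 |
| 0.88 | 0.357 | 380 | 0.453 | 315 |

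Values of n are approximate; ranges reflect repeat simulations. Shrinkage governs for C = 0.75 and 0.80, and optimism for C = 0.88. At C = 0.88 the simulated R2 is about twice the SAP's 0.1925, and it exceeds the formula's ceiling of 0.333 at both event shares.

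**The case against.** The strongest objection concerns attribution. A reader might infer that 782 is the product of the faulty R-squared. The reproduction above does not support that: 782 arises from the rate entry, and with R2 left at 0.1925 a correctly scaled rate brings it down to 624. Within the optimism criterion at e = 2.5, R2 of 0.10 to 0.30 moves n only from 825 to 730. This objection stands, with one limit. Below R2 of about 0.154 the shrinkage criterion overtakes (1,274 at R2 = 0.10), so the insensitivity does not hold for low values.

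A reader might also infer that 700 is too few. The documents do not show it. In the table only C = 0.75 at 18% events exceeds 700 or 680. If 0.88 is a C-index, the SAP's expression understates R2 and so asks for more participants, not fewer. The value 0.1925 is also close to the simulated 0.190 for C = 0.75 at 25% events. In addition, 700 was adopted below the SAP's own Riley figure, with consistency with the protein-screening calculation as the specific reason. The Riley number was therefore not what supported it.

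Third, the same SAP bullet describes the quantity as anticipated performance, so it is not established that 0.88 is an in-sample value. That is fair. The two descriptions conflict, and the SAP should say which applies.

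None of this rescues the conversion. Once the rate is on the right scale, the R-squared input determines n.

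**Conclusion.** The performance input in SAP 8.2 is wrong as written. The expression is not a conversion of an R-squared, and on the more plausible reading of 0.88 as a C-index it still omits the event share. It is not the main cause of 782.

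With the event share as a proportion and S = 0.9, the SAP's own R2 gives 624 to 707 across its three values of k. Simulated inputs give about 315 to 860 at k = 15. That range spans both 700 and 680, so the claim that overfitting is minimised is unsupported rather than refuted.

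The range rests on the assumed shrinkage target, the assumed distributions and censoring, and the chosen values of C. The direction of the error is not established. This should be corrected, but it does not by itself call the cohort size into question.

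**What to change.** In SAP 8.2:
- State what 0.88 is, where it comes from, and whether it is corrected for optimism. Delete the conversion formula and the apparent R-squared label.
- Enter a Cox-Snell R-squared obtained by simulation from an optimism-reduced C-index at a stated event share (25% planned, 17.98% observed). Show the result over a range such as C = 0.75, 0.80 and 0.88.
- Enter the event rate per year. A planned 25% over a mean of 10 years is 0.025 per person-year. The observed 153 events in 851 participants with a mean time of 6.51 years give 153 / (851 × 6.51) = 0.0276, if that mean covers all participants. Make text and code agree.
- Use one value of k throughout, and state the shrinkage target.
- Rerun, then restate the Riley figure and the sentence that 700 minimises overfitting.

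A bootstrap that repeats the whole protein search would give a better optimism correction. It is optional, because repeating about one million combinations in each resample is not a small task.

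The cost is a short recalculation and revised wording, with no new data. The restated figure may be more or less favourable than 782. The derivation cohort is already fixed at 851, so what changes is the claim of adequacy, not enrolment.

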  # Use double bracket [[3]] to extract the third element as a whole vector
  sample_sizes[[i]] <- res[[3]]
}
result_Riley <- data.frame(Parameter = parameters, SampleSize = I(sample_sizes))
'''

df_riley = pd.DataFrame(riley_data)
k_values_riley = df_riley["Parameter"].values
sample_sizes_riley = df_riley["SampleSize"].values
#####
def calculate_sample_size_epv(k, EPV, event_rate):
    events_required = EPV * k
    # Total sample size = required events / event_rate
    sample_size = events_required / event_rate
    return math.ceil(sample_size)

# Set the event rate and compute EPV-based sample sizes for different EPV values
event_rate = 0.25 # Example: 25% event rate
sample_sizes_epv_10 = [calculate_sample_size_epv(k, 10, event_rate) for k in k_values_riley]
sample_sizes_epv_11 = [calculate_sample_size_epv(k, 11, event_rate) for k in k_values_riley]
sample_sizes_epv_12 = [calculate_sample_size_epv(k, 12, event_rate) for k in k_values_riley]
# Plot everything: multiple EPV lines (no markers) plus the Riley line
plt.style.use("ggplot")
plt.figure(figsize=(6, 6))
plt.plot(k_values_riley,sample_sizes_riley,linewidth=2,marker=None, label="Riley's Method")
plt.plot(k_values_riley,sample_sizes_epv_10,linewidth=2,marker=None, label="EPV=10")
plt.plot(k_values_riley,sample_sizes_epv_11,linewidth=2,marker=None, label="EPV=11")
plt.plot(k_values_riley,sample_sizes_epv_12,linewidth=2,marker=None, label="EPV=12")
plt.axhline(y=700, color='red', linestyle='--', linewidth=2, label='700 People')
plt.axvline(x=15, color='blue', linestyle='--', linewidth=2, label='15 markers')
plt.xlabel("Number of Candidate Predictors (k)")
plt.ylabel("Required Total Sample Size")
plt.title("Sample Size Estimation: Riley's Method vs. EPV Rule")
plt.legend(title="Method")
plt.grid(True)
plt.show()

```

[figure not shown]

### Sample Size Estimation Using Riley's Method and the EPV Rule.

The figure illustrates the required total sample size for predictive modeling as a function of the number of candidate predictors ( $k$ ), estimated using both Riley's method (solid red line) and the EPV rule with different assumptions ( $EPV = 10, 11$ , and  $12$ , represented by solid black, blue, and green lines, respectively). Riley's method accounts for model performance characteristics and expected shrinkage, while the EPV rule provides a heuristic estimation based on the number of events per variable. The dashed red horizontal line indicates a reference sample size of 700 participants, and the dashed blue vertical line corresponds to a scenario with 17 candidate predictors. These reference lines aid in visualizing feasible study designs under different methodological assumptions.

